### Statistical methods

The primary analysis will follow the intention‑to‑treat (ITT) principle, including all randomized participants according to their allocated arm regardless of missing data or protocol deviations. A per‑protocol (PP) analysis will be performed as a sensitivity analysis, restricted to participants who completed the assigned intervention without major protocol violations. Baseline demographic and clinical characteristics will be summarized per arm using descriptive statistics. Means with standard deviations or medians with interquartile ranges for continuous variables, and frequencies with percentages for categorical variables. The balance between arms will be assessed descriptively.

Furthermore, the primary endpoint, regression rate of CIN1 at six months, will be compared between the two arms using the chi‑square test or Fisher’s exact test, as appropriate based on expected cell counts. An absolute risk difference with the corresponding 95% confidence interval will be reported as the primary effect measure. Additionally, the relative risk and odds ratio with 95% confidence intervals will be estimated. The same analytical approach will be applied to the secondary endpoints: regression rate at twelve months and progression rates at six and twelve months. Univariable and multivariable logistic regression models will be used to estimate odds ratios and 95% confidence intervals for regression and progression of CIN1. The multivariable model will include prespecified covariates and the model goodness‑of‑fit will be evaluated using the Hosmer‑Lemeshow test.

Furthermore, adverse events in the Moducare arm will be assessed by type and severity using descriptive statistics. Between‑arm comparison of the overall adverse event rate will be performed using Fisher’s exact test. In addition, subgroup analyses will be conducted to explore potential treatment‑effect modification: e.g., HPV status (HPV 16/18 positive vs. high-risk HPV vs. low-risk HPV) and smoking status (smoker vs. non‑smoker). These analyses are exploratory and will be interpreted with caution given the limited sample size. All statistical tests will be two‑sided with a significance level of p-value < 0.05. Statistical analyses will be performed using R (version 4.5.1; R Foundation for Statistical Computing, Vienna, Austria). All data will be stored on secure institutional servers with regular backup, and exports to statistical software will be performed via controlled, documented procedures.

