## Introduction

Human papillomavirus (HPV) is causally associated with virtually all cases of cervical cancer and its precursor lesions under the term cervical intraepithelial neoplasia (CIN), representing one of the strongest causal relationships documented in cancer epidemiology [1]. HPV-induced cervical dysplasia arises predominantly within the transformation zone and is classified histologically into low-grade cervical intraepithelial neoplasia (CIN1) and high-grade cervical intraepithelial neoplasia (CIN2/CIN3) lesions according to the Bethesda classification system, with the latter warranting excisional treatment. CIN1 lesions demonstrate transient productive HPV infection and spontaneous regression occurs in approximately 60% of cases under monitoring, while progression to CIN2 + occurs in only 11% and to cervical cancer in less than 0.5% of patients [2]. These favorable natural history data underpin current international guidelines that endorse active surveillance instead of immediate intervention for CIN1. Nevertheless, long-term follow-up data challenge the notion that the risk of progression for low grade cervical intraepithelial lesions is uniformly low. A nationwide, registry-based cohort study [3] demonstrated that the five-year cumulative incidence of CIN2+ among women with histologically proven CIN1 reaches 19%, rising to 25–26% in women with high-grade cytology or HPV16/18-positive status. These findings highlight a clinically significant subset of CIN1 patients at substantial risk of disease progression and underscore the need for interventions capable of enhancing the spontaneous regression rate of the wait-and-see approach alone.

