### Trial endpoints

The primary endpoint of the trial is to compare the regression rate of low-grade cervical intraepithelial neoplasia (CIN1), between the two arms: Wait-and-see control arm and Moducare intervention arm, at six months after randomization. Furthermore, the secondary endpoints include the comparison of regression rate of CIN1 at twelve months from randomization, the progression rate of CIN1 at six and twelve months after randomization and for safety analysis the intervention (Moducare) related adverse events at six months after randomization. All comparisons will be made between the above-mentioned arms of the trial.

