### Sample size

For power analysis of the trial a two-sided alpha level of 0.05, a statistical power of 80% and accounted for a 10% drop-out rate. Based on the results of a large recent meta-analysis [2] the spontaneous regression rate of low-grade cervical intraepithelial neoplasia (CIN1) of the Wait-and-see approach was set at 60% and in order to achieve a clinically important increase of at least 20%, the regression rate of Moducare was set at 80%, since robust RCTs are absent. The sample size was calculated using RStudio (V 4.3.3), applying the chi-square test formula for comparison of two independent proportions. Accordingly, we plan to enroll approximately 182 patients to account for anticipated dropouts and maintain the integrity of the primary endpoint analysis.

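### The multivariable logistic model planned for progression is poorly supported at about 20 events, and often not estimable if the count is nearer 3 to 7

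*Protocol article*

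**What the plan says.** Under Statistical methods, the protocol compares regression at six months by chi-square or Fisher's exact test according to expected cell counts, with the absolute risk difference and its 95% interval as the main effect measure. It extends that approach to the secondary endpoints. It then adds, for both unadjusted and adjusted analyses, that "logistic regression models will be used to estimate odds ratios and 95% confidence intervals for regression and progression of CIN1". Prespecified covariates, which the article does not list, are to enter the adjusted model, and its fit is to be judged by the Hosmer-Lemeshow test.

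Trial endpoints lists "the progression rate of CIN1 at six and twelve months after randomization" among the secondary endpoints. The Sample size section is built on regression only: the control rate "of the Wait-and-see approach was set at 60" per cent, and "the regression rate of Moducare was set at 80" per cent.

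The Introduction supplies the only progression figures. One is that "progression to CIN2 + occurs in only 11% and to cervical cancer in less than 0.5% of patients", with no follow-up length. The other is that "the five-year cumulative incidence of CIN2+ among women with histologically proven CIN1 reaches 19" per cent, with a higher figure of 25–26% for a higher-risk subset.

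**The concern.** The same modelling is prescribed for two endpoints with very different amounts of information. Regression yields plenty of women in both outcome categories. Progression within six or twelve months of CIN1 is uncommon, and nothing in the sample size was chosen to support a model for it.

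With few events, logistic regression fitted in the usual way gives odds ratios biased away from 1 and very wide intervals. If every event falls in one arm or one covariate category, an odds ratio is zero or infinite. The Hosmer-Lemeshow test is no safeguard: over the customary ten groups, 4 to 20 events means 0.4 to 2 expected events per group, too few for its chi-square reference.

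The Discussion expects lower progression in the intervention arm and suggests that fewer excisions could follow. A spurious or infinite adjusted odds ratio would therefore bear on a claim that readers will look for.

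**Working it through.** **Inputs from the protocol.** 182 women, 1:1, so 91 per arm; "a two-sided alpha level of 0.05, a statistical power of 80% and accounted for a 10% drop-out rate"; regression 60% versus 80%; progression 11% (untimed) and 19% at five years; progression assessed at six and twelve months.

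**Assumptions made here.** A constant hazard to convert the five-year figure; a progression risk ratio between 1.0 and 0.5, because the Discussion expects a reduction but gives no size; the covariates named in step 5.

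**1. The plan's own figure.** n per arm = [1.96·√(2·0.7·0.3) + 0.842·√(0.24 + 0.16)]² / 0.20² = 81.2, so 82 per arm and 164 in total. Allowing for dropout, 164/0.9 = 182.2, which agrees with the stated 182. In 164 evaluable women, regression leaves 82·0.4 + 82·0.2 ≈ 49 non-regressors.

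**2. Events at the upper end.** 182·0.11 = 20.0, or 164·0.11 = 18.0. If the rate is halved in the Moducare arm, multiply by 0.75: 15.0 or 13.5.

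**3. Events at the lower end.** With constant hazard, risk by time t years is 1 − 0.81^(t/5).
- Six months: 2.09%, giving 3.8 events in 182 or 3.4 in 164 (2.8 or 2.6 with halving).
- Twelve months: 4.13%, giving 7.5 or 6.8 (5.6 or 5.1 with halving).

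**4. Empty arm, with no covariates involved.** With m women per arm, control risk p and risk ratio r, the chance that at least one arm has no event is (1−p)^m + (1−rp)^m − (1−p)^m·(1−rp)^m.

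| Visit | m | r = 1 | r = 0.5 |
|---|---|---|---|
| Six months | 91 | 27% | 48% |
| Six months | 82 | 32% | 53% |
| Twelve months | 91 | 4% | 17% |
| Twelve months | 82 | 6% | 21% |

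In these trials even the univariable treatment odds ratio has no finite, non-zero estimate. For example, at six months with m = 82 and r = 0.5: 0.178 + 0.423 − 0.075 = 0.526. At a given control risk, a stronger treatment effect makes this more likely.

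**5. Adjusted model.** Simulation with 164 women, 800 trials per setting, and an exact check for separation. Smoking prevalence was set at 30%, three HPV groups at 30/45/25% and age as a continuous covariate, with no covariate effect on progression. The table gives the percentage of trials with at least one non-finite coefficient.

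| Expected events | Arm + smoking + age | Also HPV (two indicators) |
|---|---|---|
| 3.5 (r = 1) | 49% | 78% |
| 2.6 (r = 0.5) | 68% | 90% |
| 7 (r = 1) | 15% | 41% |
| 5 (r = 0.5) | 36% | 60% |
| 18 (r = 1) | 0.4% | 1% |
| 13.5 (r = 0.5) | 2% | 7% |

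**6. Events per coefficient.** With five non-intercept terms: 18/5 = 3.6 to 20/5 = 4.0 at the upper end, and 3.4/5 = 0.7 to 3.8/5 = 0.8 at the six-month lower end.

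**The case against.** Four points can fairly be made for the plan.

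- **The main analysis of progression already suits sparse data.** The risk difference with its interval and Fisher's exact test apply to progression as written. This stands: the logistic model is an addition, and only that addition is in question. The Fisher fallback, however, covers the unadjusted test and not the model. The caution about limited sample size concerns the subgroup analyses.
- **The low event count is not a protocol figure.** This also stands. No six- or twelve-month progression rate is given, and repeat biopsies could reveal CIN2+ missed at baseline, which would raise early counts. The 11% comes from the same meta-analysis whose 60% regression rate the sample size applies at six months, so about 20 events is a defensible reading. In the other direction, Trial design drops women who progress to CIN3 from the trial, which could lower the count depending on how they are handled.
- **The covariates are not given.** HPV status and smoking appear only as examples of subgroup factors. A reader might infer a large model built from them, but the article does not say so. The simulated percentages in step 5 therefore illustrate the problem and do not predict a rate. The empty-arm figures in step 4 need no covariates.
- **The estimator is not named.** A penalised fit would be compatible with the wording, and an unseen analysis plan may specify one. Conventional maximum likelihood is the natural reading, particularly alongside a Hosmer-Lemeshow check.

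A reader might also infer that the adjusted odds ratios will often fail to exist across the whole range of 4 to 20 events. The documents do not support that. Near 18 to 20 events failure was about 1% or less in these models, and the weakness there is overfitting and imprecision.

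**Conclusion.** The concern holds in a limited form. The modelling prescribed for progression is thinly supported even on the most generous reading of the protocol's figures: about 18 to 20 events, and about 4 per coefficient with five terms. If events are as few as the five-year incidence suggests at constant hazard, the model will often not be estimable. A non-finite coefficient then occurs in roughly 15% to 90% of trials, depending on visit, covariates and treatment effect. An empty arm alone removes the treatment odds ratio in 27% to 53% of trials at six months and 4% to 21% at twelve.

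The lower-end figures rest on the constant-hazard conversion and a risk ratio between 1.0 and 0.5; the adjusted-model figures also rest on assumed covariates. This concerns an additional analysis of a secondary endpoint. The primary comparison, with about 49 non-regressors expected among 164 women, is not affected.

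**What to change.** In Statistical methods:

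1. State that progression at six and twelve months is analysed by counts per arm, the already planned risk difference with 95% interval, and Fisher's exact test. Name a score-type interval (Newcombe or Miettinen-Nurminen).
2. Restrict the standard multivariable logistic model and the Hosmer-Lemeshow test to regression.
3. If an odds ratio for progression is to be modelled, specify Firth-penalised logistic regression with arm and at most one or two prespecified covariates, with profile-penalised intervals.

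This is a cheap improvement: a change of wording and a standard R package, which can be settled before the first outcome data. The small downside is that a full set of covariate odds ratios for progression is not reported. The change keeps the estimates interpretable but adds no power. With 82 women per arm, four events all in one arm give a two-sided Fisher p of 2·C(82,4)/C(164,4) = 0.12, so the six-month result may have to be presented as descriptive.

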Should the trial confirm our hypothesis, the implications for clinical practice would be substantial. Currently, the management of CIN1 relies exclusively on passive monitoring, which, despite its favorable overall natural history, leaves a clinically significant subset of patients at risk of progression, particularly those with HPV16/18-positive status, where the five-year cumulative incidence of CIN2 + can reach 25–26% [3]. The incorporation of an immunomodulatory supplement into the surveillance strategy could represent a paradigm shift in the management of low-grade cervical dysplasia, offering a non-invasive, well-tolerated intervention that actively promotes lesion regression. This approach could reduce the psychological burden associated with prolonged surveillance and decrease the need for subsequent excisional procedures.

On the other hand, some limitations of the MODUCIN1 trial should be acknowledged. The open-label design introduces the potential for performance and detection bias, as neither participants nor investigators are blinded to group allocation. While a placebo-controlled design would have been methodologically preferable, it was not feasible in the context of a dietary supplement trial where a truly inert placebo matching the appearance, taste, and dosing regimen of Moducare capsules was not available. Nevertheless, the use of an objective histological endpoint, assessed by colposcopy-directed biopsies that were centrally reviewed by the director of the Colposcopy Unit, mitigates the impact of observer bias on the primary outcome. Furthermore, the fact that pathological assessment of biopsy specimens is inherently blinded to treatment allocation provides an additional layer of objectivity.

Moreover, the six-month primary endpoint, while clinically practical and aligned with standard follow-up intervals for CIN1, may not capture the full trajectory of treatment effect, as some CIN1 lesions require longer periods for regression. The twelve-month secondary endpoint assessment partially addresses this limitation. Finally, adherence to a six-month oral supplement regimen is inherently challenging in dietary supplement trials [10], and the absence of an objective biomarker to confirm supplement intake (such as serum beta-sitosterol levels) means that treatment adherence will rely on patient self-report and capsule counting.

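### Adverse events get only a Fisher p-value between arms, while every other primary or secondary endpoint gets a risk difference with a 95% confidence interval

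*Protocol article*

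**What the plan says.** Trial endpoints places safety among the secondary endpoints: "for safety analysis the intervention (Moducare) related adverse events at six months after randomization". It adds that all comparisons are between the two arms.

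Statistical methods makes the absolute risk difference with 95% confidence interval the main effect measure for regression at six months, and adds the relative risk and odds ratio with intervals. It then extends this: "The same analytical approach will be applied to the secondary endpoints: regression rate at twelve months and progression rates at six and twelve months". Adverse events are not named there.

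For safety, the same section says that "adverse events in the Moducare arm will be assessed by type and severity using descriptive statistics". The between-arm part is one sentence: "Between‑arm comparison of the overall adverse event rate will be performed using Fisher’s exact test". The general rule on significance applies to it: "All statistical tests will be two‑sided with a significance level of p-value < 0.05".

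The article gives no adverse event rate, no acceptable excess and no power for safety. The Discussion looks ahead, should efficacy be confirmed, to "offering a non-invasive, well-tolerated intervention that actively promotes lesion regression".

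**The concern.** For a safety endpoint the useful question is how large an excess the data still allow. A p-value does not answer it, and a non-significant one is uninformative when the sample was not sized for harm. Here the p-value is the only between-arm safety result that the article commits to, although the section already prescribes a suitable effect measure for the other secondary endpoints.

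Tolerability carries weight in this trial. The Introduction puts spontaneous regression of CIN1 at about 60%, so many of the women taking the supplement would have regressed without it. The benefit-risk judgement needs an estimate of added harm and its uncertainty.

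**Working it through.** **Inputs from the protocol article.** 182 women, 1:1, hence 91 per arm; 10% drop-out, hence 91 × 0.9 = 81.9, about 82 per arm; regression 60% versus 80%; two-sided alpha 0.05; power 80%; Fisher's exact test for adverse events.

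**Assumed, because the documents do not give them.** A control adverse event rate of 0% to 20%, and a true excess of 10 percentage points.

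**Step 1: the plan's own sample size.** With pooled variance, no continuity correction and a mean proportion of 0.70:

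n per arm = [1.96 × √(2 × 0.70 × 0.30) + 0.842 × √(0.60 × 0.40 + 0.80 × 0.20)]² / 0.20² = 81.2, rounded up to 82.

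The total is 164, and 164 / 0.9 = 182.2, which agrees with the stated figure of approximately 182. The sizing rests entirely on regression; no safety quantity enters.

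**Step 2: how often Fisher's test misses a 10-point excess.** For n per arm, every 2×2 table (a events in control, b in Moducare) was enumerated. The miss probability is the sum of Bin(a; n, p₀) × Bin(b; n, p₀ + 0.10) over all tables with two-sided Fisher p ≥ 0.05.

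| Control rate | Moducare rate | Missed, 91 per arm | Missed, 82 per arm |
|---|---|---|---|
| 0% | 10% | 10% | 16% |
| 1% | 11% | 21% | 28% |
| 2% | 12% | 30% | 36% |
| 5% | 15% | 47% | 51% |
| 10% | 20% | 60% | 64% |
| 20% | 30% | 71% | 74% |

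The 0% row is what results if only events judged related to Moducare count, since the control arm then has essentially none. For a 5-point excess at 91 per arm, with control rates of 1%, 2% and 5%, the miss probability is 74%, 77% and 83%.

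**Step 3: what an interval would add.** Take 5/91 control and 13/91 Moducare.

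- Fisher two-sided p = 0.080.
- Difference: 14.29% − 5.49% = 8.79 points.
- Wilson 95% limits: control 2.37% to 12.22%; Moducare 8.54% to 22.92%.
- Newcombe lower limit: 8.79 − √[(14.29 − 8.54)² + (12.22 − 5.49)²] = −0.1 points.
- Newcombe upper limit: 8.79 + √[(22.92 − 14.29)² + (5.49 − 2.37)²] = +18.0 points.

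By contrast, 3/91 in each arm gives an interval of about −6 to +6 points. Both tables are non-significant, yet they leave very different excesses open. The p-value is 0.08 in one and 1.0 in the other, and neither figure tells the reader that the upper limit is 18 points or 6.

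**The case against.** The strongest reply is that nothing here is stated wrongly. Fisher's test is valid for sparse binary data, the article does not rule out an interval, and a condensed article may leave safety tables to an analysis plan that is not shown. Comparing the overall rate requires both arms' counts, so if these are published any reader can compute the interval. All of that stands, and it limits the weight of the point. It does not remove it: the article does specify a between-arm safety method, and it differs from the one specified for the other secondary endpoints.

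A reader might infer that the plan will treat p > 0.05 as proof of good tolerability. The documents do not support this. The Discussion's remark on tolerability is conditional on efficacy being confirmed, was written before any data, and is not tied to the Fisher test.

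A reader might also infer that a non-significant result is the likely outcome whenever there is a material excess. For a 10-point excess with 91 per arm, that is not so at control rates of 5% or less, where detection is more likely than not (missed 10% to 47%). Nor will a non-significant result usually come with a wide upper limit, as the 3/91 example shows.

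**Conclusion.** The point holds as an inconsistency in the choice of analysis, of modest weight. Adverse events are the one secondary endpoint with no stated between-arm effect measure or interval, in a trial sized only for regression. The size of the problem depends on a control rate that the documents do not give: with control rates of 0% to 20%, a true 10-point excess would be missed 10% to 71% of the time at 91 per arm, or 16% to 74% at 82. The 10-point excess is itself an illustrative choice, since the documents set no margin. The primary analysis and the sample size are unaffected.

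**What to change.** In the safety paragraph of Statistical methods:

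- Make the between-arm risk difference in women with at least one adverse event, with a Newcombe or other score-based 95% confidence interval, the safety effect measure.
- Tabulate adverse events by type and severity in both arms.
- Keep Fisher's p-value as a supplement.
- State that a non-significant test will not be read as evidence of no added harm.

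This takes one or two sentences and a little more analysis, with no additional patients. The downside is that the resulting safety statement may be less favourable than a bare non-significant p-value would suggest.

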### Participant retention

To minimize dropouts during the 12-month follow-up, we will implement a structured retention strategy coordinated by the primary investigator. Flexible scheduling, provision of appointment confirmations and results summaries will be offered. Contact details (phone and email) will be collected at baseline and confirmation reminders will be sent 7 days and 48 hours before each scheduled visit by SMS and email; non-responders will receive a telephone call within 7 days of a missed appointment. Participants will receive a printed schedule, a clinic contact card, and a brief leaflet explaining the importance of follow-up for their care and for study validity. Moreover, the primary investigator will register the reasons for withdrawal or missed visits, while the drop-out rate will be monitored monthly and an interim evaluation of retention will occur at enrollment midpoint, with corrective actions (extra reminders, outreach calls) if attrition exceeds the planned 10% allowance.

